## Methods/design

### Study aims

The aims of the Geriatric Emergency Department Intervention (GEDI) MOC evaluative research project are to:Test the efficacy of the GEDI MOC by comparing the outcomes of all people aged 70 years or older who presented to a South East Queensland ED before the implementation of the GEDI MOC with those in the 12 months following implementation. Outcomes measured will be: rates of ED representation within 72 h and 28 days, mortality, ED and hospital LoS, time to referral, time to disposition and hospital admission rates;Describe and explore the structures and processes required for the effective delivery of the GEDI MOC;Conduct an economic evaluation of the GEDI MOC.

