### Setting

This study is set on the Sunshine Coast of Queensland, Australia. In Australia, the current percentage of people aged 65 years and over accounts for around 14% of the population [1]. On the Sunshine Coast this percentage is expected to increase to 17% by 2031 [36]. The study will be conducted in the Nambour General Hospital, situated in the Sunshine Coast and Hospital Health Service (SCHHS). Nambour General Hospital is one of four public hospitals in the SCHHS. NGH is the base hospital containing 373 beds and the three secondary hospitals have a combined total of approximately 531 beds. All four hospitals have an ED where both adults and children are treated. The study ED has an annual presentation of 52,410 patients; 18% of whom are over the age of 70 years [36]. Locating the research in the SCHHS will provide evidence of the effectiveness and feasibility of this MOC in a regional setting.

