### Intervention

GEDI is a nurse-led, physician-championed innovative MOC that aims to reduce frail older person living in the community or RACF ED length of stay and streamline service delivery by maximising the provision of care during the patient’s ED journey. GEDI clinical nurses (CN) have a minimum of five years post registration experience and specialist expertise and/or education in both emergency nursing and care of the older person. Their role focuses on case-managing frail older persons living in the community or RACF in the ED facilitating rapid access and coordination of care through ED, hospital and community services.

There are 2.4 full time equivalent (FTE) GEDI CNs and a 0.8 FTE Clinical Nurse Consultant (CNC) employed by the ED. They cover the ED from 0700 to 1730 Monday to Friday and 0700 to 1530 on weekends. The GEDI CNC oversees the CN role, providing education, leadership, managerial oversight of the service and clinical support where needed. An ED physician provides medical leadership and together with the CNC they are responsible for research and administration.

In the ED, the GEDI team will provide early, rapid, targeted geriatric assessment of frail older persons living in the community or RACF presenting to the ED and, through careful inter-facility and interdisciplinary, management and planning, aim to prevent unnecessary admissions to hospital. In addition, the GEDI CNs provide a single point of contact for ED and RACF staff who may be having difficulty managing an older person with an acute illness. Table 1 outlines the elements included in the GEDI roles. The importance of the ED clinical experience required for the GEDI role relates to the need for GEDI CNs to optimise communication; multitask within a chaotic, fast-paced clinical environment; and be familiar with the staff, clinical pathways and protocols.

**Table 1 Tab1:** GEDI team responsibilities

GEDI Clinical Nurse Consultant	GEDI Clinical Nurse	GEDI Physician
Clinical responsibilities		
▪ Collaborative partnership with physician-champion to develop evidenced based guidelines specific to the needs of the geriatric patients and clinicians in the ED	▪ Works collaboratively with all ED staff	▪ Clinical resource and expert in geriatric emergency medicine

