##### Data collection

Data extraction will occur retrospectively via medical records audit of coded state based Health Service databases, namely Emergency Department Information Service (EDIS; Healthcare Group, CSC)® and Hospital Based Corporate Information System (HBCIS; iSoft). SCHHS Health Statistics unit provides linking of the EDIS, HBCIS and financial data providing raw data on all presentations to the ED and those admitted to hospital. The raw data will subsequently be manually cleaned to identify RACF residents based on their home addresses. This is important as RACFs often have independent living community residents at their facilities who needed to be excluded from this cohort. Independent variables that will be used to describe the sample and used to build multivariable models for outcomes are:Demographics - Age, Sex, postcodeDate and time of presentationClinical diagnosis – reason for presentation and ICD-10 code/categorySeen by GEDI team – Yes/NoAustralasian Triage Score [40]Adult Deterioration Detection System Score [41]Next of Kin/Substitute decision maker/Enduring Power of Attorney detailsTime to referral from ED arrivalTime to disposition from ED arrival

Outcome variables collected will be:Disposition - discharged home, moved to short stay area, admitted, diedED LoS – in minutesHospital LoS – in daysAll cause in-hospital mortality within 30 days of ED presentationED Re-presentations in 72 h and 28 daysTime to ED re-presentation within 28 days

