##### Data analysis

Descriptive statistics will be used to describe the intervention and control groups including frequencies, percentages, appropriate measures of central tendency and distribution. We will use survival analysis to jointly model length of stay and disposition, with the four destinations as competing risks. We will use survival analysis for ED representations with out-of-hospital mortality as a competing risk. All models will adjust for the patient level factors of gender, age, triage score, season, day of the week and time of presentation. Pre-post designs are vulnerable to confounding by other changes over time that may be attributed to the intervention [39]. To control for this, we will include a linear trend (based on date) in all models to account for gradual changes that are not captured in the individual variables, e.g., experience of healthcare workforce. We will also adjust for season using a sinusoid with an annual cycle to control for the winter peak in morbidity [42]. The survival analyses will use Cox models and we will check the proportional hazards assumption. The models’ residuals will be checked for outliers and correlation over time. We will calculate Cook’s influential statistic and examine relatively large outliers. We will calculate the variance inflation factor and remove variables with a score above five on the basis that they are co-linear. The key outcome will be the mean effect of the intervention together with 95% confidence intervals. The results will be reported using the Strengthening the Reporting of Observational Studies in Epidemiology (STROBE) guidelines [43].

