##### Data analysis

A multivariate cost function will be estimated to determine average cost per patient, for before- and after-GEDI MOC scenarios. The function takes into account important determinants of individual cost such as age, severity, length of stay and procedures received while in the ED. In the cost effectiveness analysis, we will estimate the average difference in number of admissions for the before- and after-GEDI scenarios. The number of avoidable admissions will be converted to cost savings using the results of the cost analysis above, and compared against the implementation cost for the GEDI MOC. If the cost savings is larger than the implementation cost, the GEDI MOC can be viewed as cost effective.

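### The joint model ends follow-up at the move to short stay, so its admitted result measures direct ED-to-ward transfer rather than hospital admission

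*Protocol article*

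**What the plan says.** In the protocol article, the Data collection section of Study 1 defines the disposition outcome by four categories: "discharged home, moved to short stay area, admitted" and died. The Data analysis section of Study 1 then commits to "jointly model length of stay and disposition, with the four destinations as competing risks", and adds: "The survival analyses will use Cox models and we will check the proportional hazards assumption".

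The Study aims section names among the outcomes "time to referral, time to disposition and hospital admission rates". The Intervention section says that the GEDI team will "aim to prevent unnecessary admissions to hospital". In the outcome list of Study 1, admission appears only as one category of disposition, and the only model named for disposition is the four-way one.

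The linkage of ED and inpatient systems is described as "providing raw data on all presentations to the ED and those admitted to hospital". In Study 3, "we will estimate the average difference in number of admissions for the before- and after-GEDI scenarios", and avoided admissions are then converted to savings.

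The article does not give the share of patients who go to short stay, does not describe any step from short stay to a later destination, and does not say when the ED LoS clock stops.

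**The concern.** In a competing-risks Cox model, the first of the listed events ends the patient's follow-up and precludes the others. A patient who goes to short stay and reaches a ward some hours later is therefore a short-stay event and never an admission. Short stay is a stage on the way: the patient still has to go home, go to a ward or die.

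The question that the model answers (how do patients first leave the ED?) thus differs from the question in the aims (are fewer older people admitted to hospital?). GEDI works on disposition and on time in the ED, so the service could itself change the use of short stay. So could a change in the area's capacity or rules between 2012 and 2015-16. Either could lower the recorded admitted share while final destinations change less, or not at all.

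**Working it through.** The article gives no short-stay rate and no power calculation, so there is no figure of its own to reproduce. What follows is an illustration with assumed inputs.

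**Inputs**
- Presentations per period: the Setting section says "The study ED has an annual presentation of 52,410 patients; 18% of whom are over the age of 70 years". 52,410 × 0.18 = 9,433.8, about 9,434.
- Admission share: about 60%. The Background section gives this as a literature figure, not as a figure for the study ED, so it serves for illustration only.
- s, the percentage points of presentations that move from direct admission to short stay between the periods: not given; assumed 2 to 10.
- p, the fraction of those patients later admitted to a ward: not given; assumed 0.3 to 1.

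**Formulas**
- Recorded change in the admitted share = −s
- True change in ward admission = −s(1 − p)
- Artefact (the part of the recorded fall that is not real) = s − s(1 − p) = s × p

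**Results, artefact in percentage points**

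| s | p = 0.3 | p = 0.5 | p = 0.6 | p = 1 |
|---|---|---|---|---|
| 2 | 0.6 | 1.0 | 1.2 | 2.0 |
| 5 | 1.5 | 2.5 | 3.0 | 5.0 |
| 10 | 3.0 | 5.0 | 6.0 | 10.0 |

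For s = 5 the recorded share goes from 60% to 55%. The true share stays at 60% if p = 1, and is 57.5% if p = 0.5. At p = 1, if the overall rate of leaving the ED is unchanged, the cause-specific hazard ratio for admission is 55/60 = 0.92 with no real effect. With p = 0 there is no artefact at any s.

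**Comparison with sampling error.** The unadjusted 95% half-width for 60% against 55% is 1.96 × √[(0.60 × 0.40 + 0.55 × 0.45)/9,434] = 1.96 × 0.00719 = 0.0141, or 1.4 points. This treats presentations as independent and ignores the covariates and the linear trend, which would be expected to widen it. On this crude scale an artefact of 2.5 to 5 points could pass for a clear effect, while s = 2 with p = 0.3 (0.6 points) lies within the noise.

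**ED LoS.** Suppose that the clock stops at the move, and let r be the time to the move relative to the ED time that the patient would otherwise have had. The mean then changes by −s(1 − r). For s = 10% and r = 0.5 this is −5%; for r = 1 it is 0. The article fixes neither the clock nor r.

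**With admission taken from final destination**, the artefact in the admission rate is 0 for every s and p.

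**The case against.** The strongest reply is that competing risks need mutually exclusive first events, not permanent end states. For time in the ED, the event is leaving the ED, and the four categories are ways of leaving it. That is a coherent model, and this part of the reply stands: the four-way model is sound for ED stay. It does not show that the same model measures hospital admission.

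A second reply is that a shift would not be hidden, because short stay is its own event and its result would rise as the admitted result falls. That also stands. A reader of both results would be warned, but could not tell from them how many short-stay patients were later admitted.

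Third, bias needs short-stay use to differ between the periods, and the article reports no such difference. This is correct, and the point is a vulnerability rather than a demonstrated bias. The planned safeguards cover it only in part: the record of system changes runs during the intervention, and the linear trend is aimed at gradual change rather than a step.

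Two stronger readings are tempting, and the article supports neither. A reader might infer that ED LoS must fall when patients pass through short stay. That requires the clock to stop at the move, and the move to come earlier than the exit would have; neither is stated. A reader might also infer that the error passes into the Study 3 savings. Study 3 draws on HBCIS, which holds inpatient episodes, and nothing says that its admissions are counted from the ED disposition code. Similarly, the admission rate in the aims may be meant to come from the linked inpatient record; the article does not say.

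**Conclusion.** The point holds for the admission effect taken from the joint model. As written, that effect concerns direct transfer from ED to ward and misses ward admissions after short stay, so it does not match the aim of preventing hospital admissions. The possible artefact is s × p: 2.5 to 5 points for an assumed shift of 5 points with half to all of those patients later admitted, and under 1 point for a shift of 2 points with p = 0.3. Both inputs are assumptions. The effects on ED LoS and on Study 3 are conditional on definitions that the article leaves open. This is an inexpensive improvement to a stated analysis rule. It does not show that the planned comparison is biased.

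**What to change.** - Keep the four-way first-exit model for ED LoS.
- Base the admission effect on final destination after ED plus short stay (home or RACF, inpatient ward, died), derived from the planned EDIS-HBCIS linkage. Alternatively, model short stay as an intermediate state with onward transitions.
- State whether the LoS clock stops at the move to short stay, and whether a stay there counts by itself as an inpatient admission in HBCIS.
- Report short-stay use in each period, with the share later admitted.
- Use the same admission definition for the admission count in Study 3.

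The cost is some recoding of data that will already be linked, and a few sentences of definition. The resulting admission figure may differ from the one given by the routine ED disposition code, which can be reported beside it.

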##### Data analysis

Descriptive statistics will be used to describe the intervention and control groups including frequencies, percentages, appropriate measures of central tendency and distribution. We will use survival analysis to jointly model length of stay and disposition, with the four destinations as competing risks. We will use survival analysis for ED representations with out-of-hospital mortality as a competing risk. All models will adjust for the patient level factors of gender, age, triage score, season, day of the week and time of presentation. Pre-post designs are vulnerable to confounding by other changes over time that may be attributed to the intervention [39]. To control for this, we will include a linear trend (based on date) in all models to account for gradual changes that are not captured in the individual variables, e.g., experience of healthcare workforce. We will also adjust for season using a sinusoid with an annual cycle to control for the winter peak in morbidity [42]. The survival analyses will use Cox models and we will check the proportional hazards assumption. The models’ residuals will be checked for outliers and correlation over time. We will calculate Cook’s influential statistic and examine relatively large outliers. We will calculate the variance inflation factor and remove variables with a score above five on the basis that they are co-linear. The key outcome will be the mean effect of the intervention together with 95% confidence intervals. The results will be reported using the Strengthening the Reporting of Observational Studies in Epidemiology (STROBE) guidelines [43].

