## Background

Across the developed and developing world the population is ageing. In Australia it is predicted that, compared to 2005 the proportion of the population over 65 years of age will increase from 13% to 24%, by 2036 [1]. With this increase, the demand on Emergency Department (ED) services by older persons living in the community or in residential aged care facilities (RACF) will increase [1–3]. A systematic review of 27 studies from around the world has demonstrated that the rate of transfer to EDs from RACFs is 0.1–1.5 transfers per RACF bed/year [4].

As a result of this ageing of the population it is imperative that the health care system develop safe models of care (MOC) that span both the community and hospital health care sectors. While the ED is uniquely designed to care for the critically ill or injured, it is often a suboptimal environment for the provision of care to the frail, older person [5, 6]. Prior research shows that older persons who develop an acute illness or who have an acute exacerbation of a chronic condition, have complex medical needs and the doctors and nurses who manage their initial care in the ED often have limited experience in geriatric medicine [7, 8]. Several studies have shown that this situation leads to: under-triage; higher rates of admission; delayed and fragmented care; longer stays in the ED; and unnecessary investigations and invasive interventions [9–19]. For patients from RACFs this is particularly true. During admission to hospital, patients from RACFs are at high risk of complications such as delirium, urosepsis, falls and death [20–22]. Patients from RACFs who develop an acute illness or an exacerbation of a chronic condition also suffer high rates of re-presentation to the ED and subsequent re-admission to hospital [2, 10, 12, 14].

Several studies indicate that a large percentage of frail older persons living in the community or RACFs express a preference for treatment in their home if appropriate [23, 24]. Despite this, approximately 60% of ED presentations lead to hospital admission [25, 26]. In an attempt to keep frail older persons at their place of residence during an acute illness, several MOC have been designed and tested. Broadly, the different MOC are divided into those that: i) provide in-home care or outreach of services from one service to another [12, 24, 27, 28]; ii) provide prioritisation or geriatric focused care in the ED [29–32]; or iii) support or enhance primary care [28, 33].

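### The one stated length-of-stay model fits ED stay only, and comparing hospital stay among admitted patients conditions on admission, which GEDI aims to change

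*Protocol article*

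**What the plan says.** The Study aims section of the protocol article lists among the outcomes "mortality, ED and hospital LoS, time to referral, time to disposition and hospital admission rates". Hospital LoS appears again in the research questions under Study design, and as a variable in days under Study 1, Data collection.

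The Study 1 Data analysis section gives one analysis for length of stay: "We will use survival analysis to jointly model length of stay and disposition, with the four destinations as competing risks". It does not say whether ED or hospital stay is meant. It adds "The survival analyses will use Cox models and we will check the proportional hazards assumption" and "The key outcome will be the mean effect of the intervention together with 95% confidence intervals". All models adjust for sex, age, triage score, season, day of the week, time of presentation and a linear trend.

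The four destinations are defined under Data collection as the values of disposition: home, the short-stay area, admission, and death. All-cause in-hospital death within 30 days of presentation is a separate outcome and is not tied to hospital LoS.

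The Intervention section says that the GEDI team will "aim to prevent unnecessary admissions to hospital". The linked data are described as "providing raw data on all presentations to the ED and those admitted to hospital".

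**The concern.** The four destinations are mutually exclusive exits from the ED, and admission is itself one of the end states. That works for ED LoS in minutes. It does not work for hospital LoS in days, because patients with an inpatient stay essentially all share the destination of admission. No other length-of-stay analysis is stated, and no rule gives non-admitted patients a value of zero. A comparison of hospital LoS therefore falls, in effect, on admitted patients.

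Admission is decided after GEDI has acted, and GEDI aims to change it. The Time 2 admitted group is thus selected by the intervention. The listed covariates describe the patient and the timing of arrival; they do not undo that selection. If the averted admissions are mainly short ones, the remaining stays are longer on average although no retained stay was lengthened. The result could then read as harm on hospital LoS while the hospital uses fewer beds.

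A lesser concern is that a ward death on day 1 and a discharge home on day 1 both appear as an admission lasting one day. More early deaths would read as shorter stays.

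**Working it through.** The article states no LoS figure, sample size or power, so there is no figure of its own to reproduce. The calculations below are illustrations.

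**Inputs from the article.** Setting: "The study ED has an annual presentation of 52,410 patients; 18% of whom are over the age of 70 years". Background: "approximately 60% of ED presentations lead to hospital admission". Hence 52,410 × 0.18 ≈ 9,434 presentations and 9,434 × 0.60 ≈ 5,660 admissions a year. The 60% is a background figure from the literature, not from this hospital. It affects absolute counts only; the percentages below do not depend on it.

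**Assumed inputs.** Mean LoS m, share of admissions averted f, and mean LoS of the averted stays s.

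**Selection through admission.**
- LoS per admission afterwards = (m − f·s)/(1 − f)
- Relative change in bed-days = −f·s/m
- Bed-days per presentation = 0.60 × (m − f·s)

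With m = 6, f = 0.10 and s = 2, LoS per admission is (6 − 0.2)/0.9 = 6.44 days, or +7.4%. Bed-days change by −0.2/6 = −3.3%, about 5,660 × 0.10 × 2 ≈ 1,130 days. Bed-days per presentation go from 3.60 to 3.48.

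| m (days) | f | s (days) | LoS per admission | Bed-days |
|---|---|---|---|---|
| 6 | 5% | 2 | 6.21 (+3.5%) | −1.7% |
| 6 | 10% | 2 | 6.44 (+7.4%) | −3.3% |
| 6 | 10% | 1 | 6.56 (+9.3%) | −1.7% |
| 6 | 10% | 6 | 6.00 (no change) | −10.0% |
| 6 | 10% | 8 | 5.78 (−3.7%) | −13.3% |

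Over m = 5 to 8 days, s = 1 to 2 days and f = 5% to 15%, LoS per admission rises by 3.2% to 15.4% while bed-days fall by 0.6% to 6.0%.

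**The same effect on the Cox scale.** Simulated stays were log-normal (median 4 days, sigma 0.9, 5,660 admissions per period). In the second period 45% of stays under 2 days were removed at random, which was 10.4% of admissions. The hazard ratio for end of stay was 0.91 (95% CI 0.88 to 0.95). That reads as a longer stay, although the intervention lengthened none. A second set of 30 replicates (median 3.6 days, sigma 1.0, 10% averted from stays of 2 days or less) also gave 0.91, with mean LoS +8.7% and bed-days −2.0%.

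**Inpatient death.** Take constant hazards with the discharge hazard fixed at 1/6.5 per day. If a share p of stays ends in death, mean LoS = 6.5 × (1 − p), and the all-cause end-of-stay hazard ratio between two shares is (1 − p₀)/(1 − p₁).
- p from 5% to 8%: mean LoS 6.18 to 5.98 days; hazard ratio 0.95/0.92 = 1.03
- p from 5% to 10%: mean LoS 6.18 to 5.85 days; hazard ratio 0.95/0.90 = 1.06

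The cause-specific hazard ratio for live discharge is 1.00 in both cases.

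**The case against.** The strongest reply is that the sentence on length of stay most naturally describes ED LoS, for which it is sound, and that the article simply does not spell out the hospital LoS analysis. A fuller plan may do so. This stands as far as it goes: the article does not say that the ED destinations will be applied to inpatient stays, and a reader who infers that has gone beyond the text. What remains is that hospital LoS is a named outcome, the one stated model cannot serve it, and a comparison among the admitted conditions on something the intervention targets.

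Second, admission rate and in-hospital mortality are reported alongside, so a longer LoS with fewer admissions would be visible. That helps interpretation, but it does not yield an estimate of the effect on hospital stay.

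Third, size and direction are assumed, and the simulations remove only short stays, so the rise is built in. This stands. The 10% case is also demanding. GEDI covers 5 × 10.5 + 2 × 8.5 = 69.5 of 168 hours a week (41%). If admissions were spread evenly over the week, averting 10% of all of them would mean averting about 24% of those in covered hours; daytime clustering would lower that.

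Fourth, the death effect is small, and bed-days do not cure it, since an early death also scores few days. Both points stand, and the fix allows for them.

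**Conclusion.** The point holds as a cheap improvement. The four-destination model fits ED LoS only, and hospital LoS compared among admitted patients is not a clean measure of GEDI's effect. Under the assumption that averted admissions are shorter than average, LoS per admission and bed use move in opposite directions: +7.4% against −3.3% in the central example, and +3.2% to +15.4% against −0.6% to −6.0% over the range examined.

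A reader might infer that the hospital LoS result will be biased against GEDI or will have the wrong sign. The article does not support that. It contains no LoS data, there is no distortion of mean LoS if averted stays are of average length, and LoS per admission falls if they are longer. Nor does it support treating inpatient death as a major source of error: a rise in the death share from 5% to 8–10% moves the end-of-stay hazard ratio only to 1.03–1.06. Selection through admission is the larger issue.

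**What to change.** In the Study 1 Data analysis section:

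1. State that the four-destination competing-risks model applies to ED LoS.
2. Add, as the estimate of GEDI's effect on hospital stay, inpatient bed-days of the index episode per presentation over all presentations in the sample. Score those not admitted as zero and use the same covariates. Say whether time in the short-stay area counts, since the article lists it separately from admission. Read the result beside in-hospital mortality, because early death also lowers bed-days.
3. Report LoS among the admitted as conditional on admission, with live discharge as the event and in-hospital death as a competing event. The Study 3 section says that the hospital information system (HBCIS) already holds discharge status.

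Tying bed-days to the index episode keeps one inpatient stay from being counted against two presentations.

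The cost is some wording and one extra model on data already being linked. The outcome is zero-heavy and skewed, so it needs a two-part model or a robust model for the mean, and it is less familiar to readers than LoS per admission.

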### Study design

Pragmatism will provide the philosophical paradigm for this mixed model evaluation research. This philosophical paradigm allows the researcher to focus on “what works” and provides solutions for problems utilising methods that best meet their needs and purpose [37]. The design will be underpinned by Donabedian’s structure, process and outcome evaluation of healthcare framework [38].

The three studies included in this protocol will aim to answer the following evaluative research questions:What is the effect of the introduction of the GEDI MOC on the outcomes of frail older persons living in the community or RACF who present to ED? (Outcomes include: rates of ED representation within 72 h and 28 days, mortality, ED and hospital LoS, time to referral and hospital admission rates).What structures and processes are required to deliver the GEDI MOC?Specifically:What are the experiences of staff in regards to the processes of the GEDI MOC?What processes pertaining to the GEDI MOC have affected the day to day operation of the ED, and how?What are the residents’ and carers’ experiences of the GEDI MOC?
What is the effect of the GEDI MOC on hospital and health service delivery costs?Specifically:What is the effect of the introduction of the GEDI MOC on per patient cost associated with ED and hospitalisation?What is the effect of the introduction of the GEDI MOC on preventing the costs associated with avoidable inpatient admissions?

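### The admission hazard ratio mixes how fast patients leave the ED with where they go, so read alone it does not answer the admission-rate question; an adjusted effect on the proportion admitted should be reported

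*Protocol article*

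**What the plan says.** Study design, research question 1, lists among the outcomes "ED and hospital LoS, time to referral and hospital admission rates"; the Study aims section also names admission rates. The Intervention section gives GEDI two purposes that matter here. It "aims to reduce frail older person living in the community or RACF ED length of stay", and the team will "aim to prevent unnecessary admissions to hospital".

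Study 1, Data collection, records one disposition per ED presentation: "discharged home, moved to short stay area, admitted", or died. ED stay is recorded in minutes.

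Study 1, Data analysis, handles both outcomes with one model: "We will use survival analysis to jointly model length of stay and disposition, with the four destinations as competing risks". On the type of regression it says: "The survival analyses will use Cox models and we will check the proportional hazards assumption". All models adjust for patient factors, season, day, time of presentation and a linear trend. On reporting it says: "The key outcome will be the mean effect of the intervention together with 95% confidence intervals". It does not say whether the hazards are cause-specific or subdistribution, or on what scale the effect will be given. The same section promises descriptive frequencies and percentages. Study 3, Data analysis, separately plans a before-after difference in the number of admissions. No adjustment is stated for either.

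**The concern.** A cause-specific Cox model for admission estimates the rate at which patients still in the ED leave it by being admitted. That rate rises if patients are processed faster and falls if fewer are destined for a ward. An intervention that works as intended here does both, so the two effects partly or wholly cancel in the hazard ratio, or one outweighs the other.

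The difficulty therefore arises when GEDI succeeds. A reader shown an admission hazard ratio above 1 would naturally conclude that GEDI increased admissions, although the proportion admitted may have fallen. The proportion is what the research question asks about and what a hospital deciding on the service needs. The article names no adjusted estimate on that scale.

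**Working it through.** The article gives no sample size, event count or hazard ratio, so there is no figure of its own to reproduce. The check asks whether the hazard ratio and the proportion admitted can point in opposite directions under modest effects.

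**Inputs**
- Baseline proportion admitted, p0 = 60%: a literature figure in the Background, not the study ED's own rate.
- Proportion admitted under GEDI, p1 = 55%: assumed.
- Shortening of mean ED stay by 10% or 20%: assumed.
- Constant hazards: assumed.

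**Formula.** With constant cause-specific hazards, mean stay = 1 / (sum of hazards) and P(admitted) = admission hazard / (sum of hazards). Hence admission hazard = P(admitted) / mean stay. With baseline mean stay set to 1:

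- Stay 10% shorter: HR = (0.55 / 0.90) / 0.60 = 1.02
- Stay 20% shorter: HR = (0.55 / 0.80) / 0.60 = 1.15

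Under these assumptions the hazard ratio exceeds 1 whenever the relative reduction in stay is larger than the relative reduction in admissions, here 1 − 0.55/0.60 = 8.3%.

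**The other destinations.** In the 20% case, the hazard ratio for all non-admission exits is (0.45 / 0.80) / 0.40 = 1.41. Combining the two recovers the proportion: 0.60 × 1.146 / (0.60 × 1.146 + 0.40 × 1.406) = 0.6875 / 1.25 = 55%. The information is in the joint model, but not in the admission hazard ratio alone.

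**A second example, built from the hazards.** Assume a baseline split of 60% admitted, 25% home, 14% short stay and 1% died. Multiply the admission hazard by 1.1 and the home and short-stay hazards by 1.4. The sum is 0.66 + 0.546 + 0.01 = 1.216, so the proportion admitted is 0.66 / 1.216 = 54.3% and mean stay falls by 1 − 1/1.216 = 18%. The admission hazard ratio is 1.10 while admissions fall by 5.7 points.

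**Dependence on the baseline.** With two causes and the same ratios (1.1 and 1.4), baselines of 40%, 50% and 70% fall to 34%, 44% and 65%. For 40%: 0.44 / (0.44 + 0.84) = 34%. The reversal does not rest on the 60%.

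**At the study's volume.** The Setting section implies about 52,410 × 0.18 = 9,434 presentations a year. One simulated, unadjusted data set of that size per period, from the second example, gave a cause-specific hazard ratio of 1.12 (95% CI 1.07 to 1.16) and a risk difference of −4.8 points (95% CI −6.2 to −3.4). Both intervals exclude no effect, on opposite sides.

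**If the model is a subdistribution (Fine-Gray) one.** On the same data its hazard ratio was 0.92 (95% CI 0.88 to 0.95), the right direction. When all exits were speeded up strongly, with 57% admitted as the target, it also went above 1: 1.05 at 1.5 times the speed and 1.10 at twice. These two figures run somewhat high, because the simulated reference period drew 58.7% admitted rather than its true 60%. The reversal at 1.5 times is marginal; the one at twice is clearer.

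**The case against.** A reader might infer that the planned model is unable to answer the admission question. The documents do not support that. The model covers all four destinations jointly, and together the four hazards determine the cumulative incidence of admission, as the working shows. Someone who read the whole output in the 20% example would see 1.15 for admission against 1.41 for other exits, which is the pattern of a lower admission share.

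The article also never fixes a hazard ratio as the reported measure and never says cause-specific. A condensed article may leave both to the analysis plan. This stands, and it limits the point to the measure reported. It does not remove it: the article names this model as the adjusted analysis and does not commit to turning it into a proportion. A subdistribution model is only a partial escape.

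A reader might also infer that the economic study inherits the problem. It does not: Study 3 states its own difference in admissions and does not draw on the Cox model. That difference and the descriptive percentages do address the admission rate, but with no stated adjustment neither replaces an adjusted effect in Study 1.

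Finally, the phrase "The key outcome will be the mean effect of the intervention together with 95% confidence intervals" might be read as promising something that a Cox model does not produce, or as inviting a multiplicity calculation across the listed outcomes. The phrase can simply mean a point estimate with its interval, and the section announces no significance tests. Neither reading is needed here.

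**Conclusion.** The point holds in limited form. Because GEDI is meant to change both the speed and the destination of ED exits, a cause-specific admission hazard ratio is a poor summary of its effect on admission rates and can have the opposite sign. In the illustration it is 1.02 to 1.15 while admissions fall from 60% to 55%.

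Those values rest on constant hazards, a literature baseline and assumed effects. They show that reversal needs only modest changes, not that it will occur in this study. The exact 8.3% threshold belongs to the constant-hazards case. The model is sound as a supporting analysis. What the article lacks is a commitment to an adjusted effect on the scale of the question. This is an inexpensive improvement rather than a fatal flaw.

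**What to change.** State in Study 1, Data analysis, that the effect on admission will be reported as an adjusted risk difference and risk ratio with 95% confidence intervals. Either of two routes will do:

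- a binary regression of recorded disposition (admitted versus the other three destinations) on period and the same covariates, for example logistic regression with standardisation or modified Poisson regression; or
- adjusted cumulative incidence of admission by period, obtained by combining all four destination hazards from the joint model.

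Report ED stay as an adjusted difference in minutes. Keep the destination-specific hazard ratios as supporting results, say whether they are cause-specific or subdistribution, and present all four together.

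The cost is a few sentences in the plan and one or two simple extra models. No new data are needed, since disposition and ED stay in minutes are already to be collected.
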